## Abstract

**Background:**

Neck and shoulder complaints are common among employees in sedentary occupations characterized by intensive computer use. Specific strength training is a promising type of physical exercise for relieving neck and shoulder pain in office workers. However, the optimal combination of frequency and exercise duration, as well as the importance of exercise supervision, is unknown. The VIMS study investigates in a cluster randomized controlled design the effectiveness of different time wise combinations of specific strength training with identical accumulated volume, and the relevance of training supervision for safe and effective training.

**Methods/design:**

A cluster randomized controlled trial of 20 weeks duration where employed office workers are randomized to 1 × 60 min, 3 × 20 min, 9 × 7 min per week of specific strength training with training supervision, to 3 × 20 min per week of specific strength training with a minimal amount of training supervision, or to a reference group without training. A questionnaire will be sent to 2000 employees in jobs characterized by intensive computer work. Employees with cardiovascular disease, trauma, hypertension, or serious chronic disease will be excluded. The main outcome measure is pain in the neck and shoulders at week 20.

**Trial Registration:**

The trial is registered at ClinicalTrials.gov, number NCT01027390.

## Background

Musculoskeletal disorders cause poor work ability and lost working days [1], and constitute a third or more of all registered occupational diseases [2,3]. Among the general population, back and neck pain are the most prevalent types of musculoskeletal disorders, and represent a major socioeconomic burden in terms of sickness absence compensation, disability pension, and health services [4]. Development of neck, shoulder and arm complaints are common in sedentary occupations characterized by intensive computer use [5-7]. Considering the rapid growth of computer-use at all levels of society the problem does not appear to diminish.

Physical exercise is a cornerstone in health and well-being [8]. An increasing number of studies and reviews within the last decade provide evidence for the effectiveness of physical exercise at the workplace in managing musculoskeletal pain [9-12]. While specific strength training of the neck and shoulders is the most promising type of physical exercise for relieving neck pain [13-16], evidence is lacking for the effect of such training on shoulder pain [10]. One study showed effectiveness of a home exercise program in reducing shoulder pain in construction workers [17], but further randomized controlled trials are needed to evaluate the effect of workplace exercise interventions on shoulder, arm and wrist pain [10].

International health guidelines recommend adults to perform at least 30 minutes of moderate physical activity 5 days per week for general health [18]. While these guidelines are based on prevention of metabolic syndrome related disorders, the optimal duration and frequency of physical exercise for proper musculoskeletal function remains to be established. Previous studies on rehabilitation of neck and shoulder pain typically used training frequencies of three times per week with a duration of 20 to 60 minutes per training session [13-16]. However, physiological adaptations in healthy adults can be achieved both in response to long exhausting bouts of resistance training with several days of rest in between and in response to shorter bouts performed several times a week [19]. One study with healthy adults comparing the effect two versus three strength training sessions per week - with equal weekly volume - found similar gains in muscle mass and strength [20]. A meta-analysis - based on 177 resistance training studies - showed that three training days per week is optimal for efficient strength gains in untrained healthy adults without musculoskeletal disorders [21]. By contrast, adherence - at least in weight loss programs - seems to be higher when multiple short bouts of exercise are carried out as opposed to fewer and longer bouts [22]. However, no previous studies have determined the optimal combination of duration and frequency of exercise for relieving pain of the neck and shoulder. Resolving these research questions are important, to thereby allow companies a more flexible and efficient integration of exercise at the workplace.

Most studies investigating the effect of exercise for neck and shoulder pain have used supervision by experienced training instructors or physiotherapists [13-16]. However, this may in practice not be an available resource at most workplaces. Studies investigating the effect of unsupervised training at the workplace on musculoskeletal pain have typically reported small or insignificant treatment effects [10]. Thus it is necessary to determine the minimal amount of supervision needed to effectively implement exercise at the workplace.

This study - Work place Adjusted Intelligent physical exercise reducing Musculoskeletal pain in Shoulder and neck (VIMS) - investigates in a cluster randomized controlled design

1) the effect of different time wise combinations of training with identical accumulated duration, in order to elucidate possible ranges of training effectiveness and flexibility

2) the relevance of training supervision for safe and effective training, in order to minimize expenses for workplace physical exercise training.

The concept of 'intelligent physical exercise' is to balance the physiological capacity relatively to occupational exposure, tailor the exercise to individual capacities and disorders, allow for flexibility and interest for the participant, and to be as cost-effective for the company as possible.

## Methods and design

### Study design

We are currently conducting a cluster randomized controlled trial in Denmark. The trial began in February 2010 and ends in June 2010. The participants were recruited from 12 geographically different units located in all major cities throughout Denmark balanced according to the population density with around half in the Copenhagen area and half in other parts of Denmark. The criteria were that the sites should be distributed across the country, they should be so large that it was possible to randomize naturally occurring clusters to five groups and the total number of employees in the sites should be around 2000 persons.

All of the participants gave their written consent to participate in the study. The local ethics committee approved the study protocol (H-C-2008-103), which qualified for registration in the ClinicalTrials.gov, number NCT01027390

### Study population

Figure 1 shows the flow of participants. We invited 2114 employees to participate in the study. A short introduction and invitation text, together with a link to an internet-based questionnaire on current working conditions, health and symptoms, physical activity etc. (for details see below) went out to the prospective participants by email. Out of the invited employees, 990 replied to the questionnaire. Table 1 shows that employees (men and women separately) who accepted (yes) and declined (no) participation were broadly similar with regard to gender, age, height, and body mass. However, employees accepting participation had a higher 12-month prevalence of musculoskeletal symptoms in the neck and shoulders, and higher pain intensity in the neck and shoulders during the previous 3 months.

**Table 1 T1:** Characteristics of employees who accepted (yes) and declined (no) participation in the intervention.

	Women (N = 570)			Men (N = 420)		
	Yes	No	p - value	Yes	No	p - value
Age (years)	44 (11)	42 (12)	0.04	49 (9)	48 (11)	0.19
Height (cm)	168 (6)	170 (6)	0.01	184 (6)	183 (6)	0.61
Weight (kg)	70 (13)	69 (12)	0.62	90 (13)	88 (11)	0.42
BMI (kg m^-2^)	25 (4)	24 (4)	0.09	27 (3)	26 (3)	0.47
Neck pain intensity previous 3 months (scale 0-9)	3.8 (2.3)	2.5 (2.4)	<.0001	2.7 (2.3)	1.7 (2.0)	<.0001
Shoulder (right) pain intensity previous 3 months (scale 0-9)	2.6 (2.5)	1.6 (2.1)	<.0001	1.9 (2.3)	0.8 (1.5)	<.0001
Shoulder (left) pain intensity previous 3 months (scale 0-9)	2.1 (2.4)	1.3 (2.0)	<.0001	1.4 (2.1)	0.6 (1.4)	<.0001
12-month prevalence of neck pain	94%	78%	<.0001	85%	63%	<.0001
12-month prevalence of right shoulder pain	73%	53%	<.0001	59%	35%	<.0001
12-month prevalence of left shoulder pain	64%	41%	<.0001	49%	26%	<.0001

P-values denote significance levels between those accepting and declining participation, separately for women and men.

**Figure 1 F1:**
[figure not shown]
**Flow-chart**. 1WS: one weekly session with supervision, 3WS: 3 weekly sessions with supervision, 9WS: 9 weekly sessions with supervision, 3MS: 3 weekly sessions with minimal supervision. Reference: reference group without training

Exclusion criteria were (i) hypertension (Systolic BP >160, diastolic BP > 100) or cardiovascular diseases, (ii) symptomatic herniated disc or severe disorders of the cervical spine, (iii) postoperative conditions in the neck and shoulder region, (iv) history of severe trauma, and (v) pregnancy, (vi) or other serious disease. Prospective participants had to work at least half of their working hours in an office environment to be included. The remaining 573 participants were randomly allocated at the cluster level to five groups as described below. Table 2 shows the baseline characteristics of the included participants of the five groups. After the cluster randomization, workers were excluded if they contracted a condition included in the aforementioned exclusion criteria or if they were on maternity leave or on other long-term absences (men and women).

**Table 2 T2:** Characteristics of the five groups.

	1WS (N = 115)	3WS (N = 122)	9WS (N = 113)	3MS (N = 126)	Reference (N = 97)
Age (years)	47 (11)	47 (11)	46 (10)	45 (11)	46 (10)
Height (cm)	174 (9)	174 (10)	175 (9)	175 (10)	175 (10)
Weight (kg)	77 (15)	76 (18)	77(14)	78 (16)	80 (16)
BMI (kg^.^m^-2^)	25 (4)	25 (4)	25 (4)	26 (4)	26 (5)
Neck pain intensity previous 3 months (scale 0-9)	3.3 (2.2)	3.2 (2.4)	3.1 (2.3)	3.3 (2.3)	3.2 (2.3)
Shoulder (right) pain intensity previous 3 months (scale 0-9)	2.2 (2.3)	2.3 (2.4)	1.9 (2.2)	2.0 (2.4)	2.0 (2.3)
Shoulder (left) pain intensity previous 3 months (scale 0-9)	1.5 (2.1)	1.7 (2.2)	1.8 (2.2)	1.6 (2.2)	1.4 (1.8)
12-month prevalence of neck pain	89%	89%	88%	92%	90%
12-month prevalence of right shoulder pain	69%	69%	63%	66%	62%
12-month prevalence of left shoulder pain	54%	58%	59%	56%	53%

1WS: one weekly session with supervision, 3WS: 3 weekly sessions with supervision, 9WS: 9 weekly sessions with supervision, 3MS: 3 weekly sessions with minimal supervision. Reference: Reference group without training

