### Statistics

The primary outcome is change in pain of the neck and shoulders at 20 weeks. Secondary outcomes include the other measures mentioned above. We plan to analyze the main data according to the intention-to-treat principle. Secondly, we will also analyze data per protocol. We will use repeated measures analysis of variance. Our design allows us to compare both the effect of different combination of duration and frequency and the effect of training supervision (figure 3). The following null-hypotheses will be tested;

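### Excluding workers for events after randomisation conflicts with the intention-to-treat main analysis and can remove some whose pain worsened

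*Protocol article*

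**What the plan says.** Under Study population, the Protocol article lists the exclusion criteria, says that 573 workers were allocated by cluster to five groups, and describes those groups in Table 2. It then adds: "After the cluster randomization, workers were excluded if they contracted a condition included in the aforementioned exclusion criteria". The same sentence makes maternity leave and any other lengthy absence, in either sex, further grounds. It sets no end date for this rule. It does not say whether an excluded worker stops training, stops receiving questionnaires or leaves the analysis.

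The criteria that the rule refers back to are mixed. Some concern the region in which the outcome is measured, for example "symptomatic herniated disc or severe disorders of the cervical spine" and postoperative neck or shoulder conditions. Others are general: "i) hypertension (Systolic BP >160, diastolic BP > 100) or cardiovascular diseases", severe trauma, pregnancy and other serious disease.

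Under Statistics the outcome is defined: "The primary outcome is change in pain of the neck and shoulders at 20 weeks". The analysis is then set out: "We plan to analyze the main data according to the intention-to-treat principle". A further analysis follows: "Secondly, we will also analyze data per protocol". The section does not mention the exclusions made after randomisation.

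**The concern.** An intention-to-treat analysis keeps each randomised person in the allocated group whatever happens afterwards. A rule that removes people for a condition or an absence arising after allocation does the opposite.

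This matters most where the trigger is related to the outcome. A worker who develops a cervical disc disorder, has neck or shoulder surgery or goes on long-term sick leave may also be one whose pain has risen. The article's Background itself links back and neck pain with sickness absence. If such workers leave the analysis in different proportions across the groups, or are affected to different degrees, the groups compared are no longer those formed by randomisation. Both null hypotheses are exposed: the one on training schedules and the one on supervision.

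**Working it through.** **1. Do the exclusions come after the randomised count?** Table 2 gives 115 (1WS), 122 (3WS), 113 (9WS), 126 (3MS) and 97 (reference). The sum is 115 + 122 + 113 + 126 + 97 = 573, the number allocated. Table 2 therefore holds everyone randomised, and the later exclusions are taken from that number.

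**2. What are workers excluded from?** Three features of the text point to the study rather than to training alone.
- The sentence stands under Study population and uses the language of the eligibility criteria.
- It refers to workers without limiting the rule to the training groups. The reference group had no training to stop (The VIMS intervention program).
- Nothing in the article says that follow-up continues for excluded workers.

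**3. How large could the bias be?** Let q be the proportion excluded in an arm, and let D be how much worse, in points, the excluded workers' mean change is than that of the workers retained. The full-arm mean is then

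(1 − q) × m + q × (m + D) = m + qD,

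where m is the mean change of those retained. Exclusion makes the arm look better by qD. The bias in the difference between arms 1 and 0 is q1·D1 − q0·D0, or (q1 − q0) × D when D is the same in both. If both q and D are equal across arms, the bias is zero.

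The article gives neither q nor D, so all inputs below are assumptions:

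| Excluded, arm 1 vs arm 0 | q1 − q0 | D (points) | Bias (points) |
|---|---|---|---|
| 5% vs 5% | 0 | 1 to 3 | 0 |
| 5% vs 2% | 0.03 | 1 to 3 | 0.03 to 0.09 |
| 10% vs 5% | 0.05 | 1 to 3 | 0.05 to 0.15 |
| 10% vs 0% | 0.10 | 1 to 3 | 0.10 to 0.30 |

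The sign follows the arm that loses more of the worsened workers. Exchanging the two arms reverses it.

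**4. Against what effect?** The power statement names a 10% change in pain without saying 10% of what.
- Read as 10% of the 0–9 scale (0.9 points), the non-zero range is 0.03/0.9 = 3% to 0.30/0.9 = 33% of the effect.
- Read as 10% of a baseline neck-pain mean of 3.2 (0.32 points), it is 0.03/0.32 = 9% to 0.30/0.32 = 94%.

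The planned 150 per group plays no part in this point.

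**The case against.** The best reply is that the article never says what workers were excluded from. If it means that they stopped training while still being followed and analysed as allocated, or that they were left out of the per-protocol analysis only, there is no conflict. Analysis sets are also often defined in a fuller document. This stands as a reason to ask for clarification. It does not remove the point, because the article states the exclusion itself, in terms that also cover the untrained reference group, and sets it beside an intention-to-treat plan without explanation.

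A reader might infer more than the text supports, in four ways.
- **That the rule removes precisely those whose pain worsened.** Pregnancy, maternity leave, hypertension and cardiovascular disease need have nothing to do with neck or shoulder pain. The rule can remove some workers who worsened.
- **That it ran for all 20 weeks.** No limit is stated, but the sentence is in the past tense in an article written while the trial was under way. Sequel to the randomization shows that there was an interval between randomisation and the start of training. The removals may belong to that interval, in which case they could not be consequences of training.
- **That it favours training because instructors detect more conditions.** The 3MS group was supervised only in the initial week, all five groups were tested at the start, midway and at the end, and the reference group answered the same questionnaires. Nothing says that instructors identify or decide exclusions.
- **That events are concealed.** The flow chart is not shown in the copy reviewed, and nothing says that exclusions go unreported.

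**Conclusion.** The point holds as a conflict between two stated parts of the plan. On its natural reading, the rule under Study population drops randomised workers for events after allocation, and the intention-to-treat principle under Statistics does not allow that. Because some triggers can be related to the primary outcome, the rule may bias the arm comparisons.

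Neither direction nor size can be established from the article, since counts, timing and reasons by arm cannot be read. The figure of 0.03 to 0.30 points is an illustration under assumed exclusion rates and severity, and zero is also possible. The conclusion rests on reading the exclusion as removal from the study. If something narrower was meant, the sentence still needs to say so.

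**What to change.** Reconcile Study population with Statistics by stating that:
- contracting a listed condition, or being on maternity leave or other long-term absence, after randomisation does not remove a worker from questionnaire follow-up or from the intention-to-treat set;
- all 573 randomised workers are analysed in their allocated cluster and group, using all available data;
- exclusions on these grounds apply only to the per-protocol analysis;
- the number, timing and reasons of such events are reported for each of the five groups.

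Who may continue to train is a clinical matter for the investigators, and this change does not touch it.

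The cost is small: continued email questionnaires to the affected workers, of the kind the untrained reference group already answers, and a possibly slightly smaller effect estimate. The article describes the trial as still running, so the analysis set can be fixed before the analysis.

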### Procedure of the cluster randomization

Work place physical exercise has implicit social elements of both getting together, competition and group pressure. For the intervention to capture these elements, we used cluster as the unit of randomization. The clusters were naturally occurring groups of employees, thereby also minimizing contamination between clusters. To help ensure the comparability of the 4 intervention groups and the reference group, geographical sites were categorized into 13 strata. Each stratum was divided into 5 naturally occurring clusters. Building, floor, department and the size of clusters were taken into account when defining the clusters in order to attain intervention and reference groups of similar sizes in each stratum. Strata and clusters were formed by authors MZ, LA and GS. In two of the strata forming of clusters entailed individual randomization into two clusters. This individual randomization was performed by a data manger when stratum and cluster affiliation was attached to the participants.

Within each stratum the clusters were randomized to group (group was sampled with replacement and assigned to the cluster). Randomization was performed by author HF using a SAS macro based on the RANUNI function. In more details: Strata were numbered consecutively (1,...,13) and clusters numbered consecutively with strata (1,...,5). Within each stratum, the clusters were sorted according to a random number and assigned the color codes red, green, blue yellow white (a code for the 4 interventions and the reference group) in succession and cyclically. To minimize imbalance over several strata with a number of clusters no divisible by five, the SAS macro was programmed to start the cyclic assignment by assigning one of the colors at random (with probability 1/5). As the formation of clusters resulted in exactly five clusters in each stratum, this element of the macro was redundant.

### Sequel to the randomization

When the training schedules and premises were sent out, just before the start of the intervention, it appeared from the enquiries that a particular subgroup of participants had misunderstood the slightly ambiguous question concerning geographical site. The wrongly placed 43 individuals were identified by comparing questionnaire responses to staff records. Before the intervention commenced the individuals were re-allocated according to the following principles wherever possible:

▪ From the response to questions concerning departmental affiliation and floor of the building the true cluster was determined. The respondent was re-allocated to the treatment corresponding to that cluster.

▪ When ambiguity with respect to determining the right re-allocation cluster, a cluster allocation resulting in no change in treatment group was preferred.

▪ If the respondent belonged in one of the clusters detemined by individual randomisation, the cluster re-allocation was determined by flip of a coin.

### The VIMS intervention program

The four training-groups performed the same total amount of exercises and repetitions per week - i.e. an equal training volume - for a total of one hour per week for 20 weeks during working-hours. Experienced instructors supervised half of the training sessions three of the groups. The first group trained for 1 hour once a week (1WS, 1 per week, supervised), the second group trained 20 minutes 3 times a week (3WS, 3 per week, supervised) and the third group trained 7 minutes 9 times a week (9WS, 9 per week, supervised). Group four (3MS, 3 per week, minimally supervised) followed the same program as 3MS, but received supervision only during the initial week. The reference group was not offered any physical training, but replied to the same questionnaires as the intervention-groups.

The intervention-groups performed specific strength training with 5 different dumbbell exercises, as shown in figure 2, for the neck and shoulder muscles:

**Figure 2 F2:**
[figure not shown]
**Illustration of the five training exercises**; A) Front raise, B) lateral raise, C) reverse flies, D) shrugs, and E) wrist extension.

1. Front raise: From a neutral starting position the participant lifts one arm at a time to 90 degrees shoulder flexion, and 90 degrees internal rotation. The elbows are slightly flexed (~5°) during the entire range of motion.

2. Lateral raise: the participant is standing with arms in neutral starting position and the elbows are in a static slightly flexed position (~5°). The participant lifts both arms to 90 degrees shoulder abduction and 30 degrees horizontal flexion.

3. Reverse flies: The participant is sitting bent over forward with the back straight and arms hanging. The arms are raised bilaterally, while keeping the elbows in a static slightly flexed position (~5°), until the upper arms are horizontal.

4. Shrugs: The participant is standing erect with arms to the side and elevates the shoulders as high as possible in a maximal shrug.

5. Wrist extension: sitting with the forearm pronated on a support. From full palmar flexion the participant moves the wrist to full dorsal flexion

Participants performed exercises in a rotating manner to optimally increase training load, and rested 1-2 minutes between sets [19]. Each training session started by warming up for 10 repetitions with loadings of 50% of 1 repetitions maximum for each respective exercise of that day.

During the 20-week intervention training loads were progressively increased according to the principle of periodization and progressive overload. Table 3 shows that the training intensity was progressively increased from 20 repetitions maximum (RM) at the beginning of the intervention-period to 8 RM during the later phase. The first 12 weeks of the program followed the principles of linear periodization and the last 8 weeks the principles of undulating periodization, as both methods have been shown to be more efficient than non-periodized training [19].

**Table 3 T3:** Progression schedule

Week	Sets and intensities
1	15 × 20 RM
2	15 × 15 RM
3	15 × 15 RM
4	21 × 15 RM
5	21 × 12 RM
6	21 × 12 RM
7	21 × 12 RM
8	24 × 12 RM
9	21 × 10 RM
10	21 × 10 RM
11	24 × 10 RM
12	24 × 10 RM
13	6 × 8 RM, 6 × 12 RM, 6 × 15 RM
14	9 × 8 RM, 6 × 12 RM, 6 × 15 RM
15	9 × 8 RM, 6 × 12 RM, 6 × 15 RM
16	21 × 8 RM
17	9 × 8 RM, 9 × 12 RM, 6 × 15 RM
18	9 × 8 RM, 9 × 12 RM, 6 × 15 RM
19	9 × 8 RM, 9 × 12 RM, 6 × 15 RM
20	24 × 8 RM

Total number of sets per week and intensities used during the 20 week intervention period. All four training groups had the same weekly training volume. RM: repetitions maximum. For instance 15 × 20 RM should be read "15 sets with loadings of 20 repetitions maximum".

